### Randomization

An independent statistician generates a randomization list using the online resource ‘Research Randomizer’. This list is used by researchers to allocate volunteers to either the control or treatment group on a 1:1 basis. Patients are allocated their number in ascending order based on their order of enrolment. Allocation is concealed from the participant and researcher until all baseline assessments have been completed. Due to limited resources, the same researcher delivers the intervention and administers the research measures, and therefore treatment allocation cannot be concealed from the researcher. Thus, neither participants nor researchers are blinded to treatment allocation during intervention delivery or during outcome assessment. An independent statistician, who is blinded to the treatment allocation, will complete the initial analysis for the main outcomes.

### Interventions

To improve the reporting of the interventions, the Template for Intervention Description and Replication [28] and the SPIRIT (Standard Protocol Items: Recommendations for Interventional Trials) checklist and figure [29] have been used to guide the description of the interventions. The SPIRIT checklist itself is attached in Additional file 1, presenting items addressed in the reporting of the protocol overall and the SPIRIT figure is attached in Additional file 2, summarizing a schedule of enrolment, interventions, and assessments.

#### Treatment group: brief self-management mindfulness-based audios

Patients in the treatment group are given an audio recording of a 15-minute mindfulness body scan on an MP3 player (with earphones) or are offered the option of having the audio downloaded directly to a personal device of their choice, such as a smart phone or iPad.

The choice of the body scan meditation for the audio was based on successful traditional mindfulness-based stress reduction interventions, which routinely include a body scan meditation as the introductory exercise. In a clinical setting with a chronic pain population, a brief (10 minute) version of the body scan was found to reduce reports of distress, immediately after listening to the audio [27].

The body scan used in this study is an extended version of a 10-minute body scan used in a qualitative study (to be published elsewhere) investigating the acceptability of the intervention to patients. It is based on a transcript from Breathworks [30], an established mindfulness organisation specialising in supporting those with chronic pain. As part of the prior qualitative study, and in response to feedback from patients, the intervention was extended from 10 to 15 minutes so that it would feel less rushed.

The audio recording directs the listener to systematically ‘scan’ their body with their attention, starting with the toes and finishing with the crown of the head. Throughout this process, the listener is also encouraged to be aware of their breathing and to accept all thoughts and feelings, whether positive or negative, without trying to alter them in any way. This intervention is administered face-to-face for the initial use by a researcher in a clinical setting (i.e. physiotherapy/medical side room or cubicle) and telephone follow-up at one week and one month is conducted by the same researcher. Use of the audio at least three further times during the first week is requested and, after that, use is encouraged but no set number of times is prescribed for the following three weeks. Following administration of the intervention, a study packet, including information and instructions for use of the audios along with brief information regarding mindfulness (i.e. frequently asked questions) and questionnaires to be filled out at home, is given to the patient. The inclusion of an information sheet was developed in response to patient feedback in the previous qualitative study.

An audio of a breathing meditation and a moving meditation are given to the treatment group as well, but use is not recommended until after one week. The breathing meditation is an exercise where breath is used as an object of concentration and the listener is asked to focus on the sensations of breathing (e.g. the feeling of the chest rising and falling). The moving meditation is focused on gentle exercises (e.g. small wrist twists or arm movements), which can be done sitting or standing and the listener is guided to pay attention to bodily sensations after making each movement. Both are based on transcripts from Breathworks.

#### Control group: relaxation/distraction audios

Patients in the control group are given eight, 15-minute audio recordings of sequential readings from “The English Village: History and Traditions” [31], which is a non-fiction book considered to be neutral in nature. The readings start from the beginning of the book and the hope is that enough interest is generated as the story progresses, so as to encourage patients to listen to a total of four sessions in the first week as easily as those in the treatment group. In total, eight sessions were recorded with the intention that four recordings would be used in the first week and that the remaining four could be used in the following three weeks. As with the treatment group, patients are given an MP3 player (with earphones) or the option of having the audios downloaded directly to a personal device. For the first session in clinic, the first of these sequential readings, which is also the first section of the book, is presented. Non-fiction material, similar in style and content, has been used in a previous study examining the acute effects of mindfulness among those with chronic pain, where it has been found to be an acceptable intervention [27]. Recordings were made using the same narrator as the intervention, and are read at a similar pace and with comparable pauses.

As with the treatment group, use of the audios is requested at least three further times during the first week. After that, continuing use is encouraged, with no set prescription for the following three weeks. Following administration of the control intervention, the study packet, including information and instructions for use of the audios (minus the mindfulness frequently asked questions that are included for the treatment group) and questionnaires to be filled out at home, is given to the patient.

### Procedure in clinic

Patients who meet the inclusion criteria are approached by the research team and given a patient information sheet regarding the study. Patients are given as much time as they want to consider whether they want to participate and written consent is obtained from all patients who agree to do so. Delivery of the intervention is standardized, with a researcher checklist (i.e. written manual) including a step-by-step script developed to address fidelity issues. This script and checklist are used during recruitment and researchers observed each other administering the intervention to at least one patient each so as to standardize procedures.

As detailed previously, an initial face-to-face visit is conducted in a private room or cubicle at St George’s Hospital or St John’s Therapy Centre. Patients are randomized to either the control or treatment group and asked to complete baseline measures, including brief psychological measures, and to listen to the relevant audio once in clinic with the researcher. After listening to the audio, patients are asked to complete the brief psychological measures again. Before leaving, patients are advised to consider barriers and solutions to use of the audio in their own environment and are given a study packet to take home. They are instructed to use the audios as a self-management tool and to try the audio during particularly painful times if possible. The contents of the study packet containing follow-up questionnaires (i.e. Study Diaries 1–3), self-addressed prepaid return envelopes and brief instructions, are then reviewed with the patient in case there are any queries. If the audios are not directly downloaded to a personal device, patients are allowed to keep the MP3 players if they want after they finish, as they are a minimal cost. The offer of the MP3 player is not mentioned in the patient information sheet, and therefore is not considered as an incentive to recruitment.

### Measures and schedule of assessment

#### Baseline data collection

Patients are asked to provide demographic details including age, marital status, occupation, education and ethnic group along with five pain-related questions, namely: “What is your clinical diagnosis?”, “How long have you been living with your pain?”, “Are you currently taking any medication for your pain and if so, which one/s?”, “Over the last week, how confident have you been in managing your pain” (1 = not at all confident to 7 = extremely confident), and “During the past week, how much has your work or other regular daily activities been limited as a result of your pain symptoms?” (1 = not at all to 5 = extremely). They then complete a measure of mood (Hospital Anxiety and Depression Scale; HADS [32]), a mindfulness questionnaire (Cognitive and Affective Mindfulness Scale-Revised; CAMS-R [33]), a pain-specific questionnaire (Brief Pain Inventory; BPI [34]), a pain catastrophizing questionnaire (Pain Catastrophizing Scale; PCS [35]), and a health-related quality of life (HRQoL) questionnaire (EuroQol – 5 Dimension – 5 Levels; EQ-5D-5 L [36]). Immediately before and after the initial use of the audio in clinic, patients are asked to complete three questions regarding their level of distraction, pain severity and pain distress (1 = not at all to 5 = extremely). Full details of the measures are given below.

#### Measures to be completed during the first week

Study Diary 1 includes a self-monitoring table detailing date, time and position of use (e.g. sitting or lying) of the audios and a repeat of the baseline brief measures of level of distraction, pain severity and pain distress immediately before and after the last session of listening to the audio during the first week.

#### Measures to be completed after one week

Study Diary 2 includes a brief questionnaire where patients are asked: “How useful did you find the audio guide for helping you to relax?” (1 = not at all to 5 = extremely useful), and “Would you recommend this audio guide to others to help manage their chronic pain?” (1 = definitely would not recommend to 5 = definitely would recommend it). To assess level of experience of activities related to mindfulness, the question: “Have you had experience of yoga, tai-chi or any type of meditation?” (1 = no experience of these activities to 7 = I currently practice these activities at least once a week) is included. These questions are followed by a repeat of the measure of mindfulness that was completed at baseline so as to detect any early changes in mindfulness present after one week.

#### Measures to be completed during and after one month

Study Diary 3 includes another self-monitoring table where patients can continue to detail date, time and position of use of the audios during the three weeks prior to the final 1 month follow-up. At 1 month, items regarding pain self-efficacy and physical function are repeated in addition to the measures of mood, pain catastrophizing, mindfulness, and HRQoL that were administered at baseline. While one week is likely too brief for patients to make (meaningful) changes in physical and/or psychological function, assessment after the completion of the intervention (one month) will better allow for the detection of changes in function where they have occurred.

A brief assessment of whether they have continued listening to the audio (and if so, how often), a discussion of the main barriers to and facilitators of use, and their view on the beneficiality of an online support group forum, texting support and more face time, is conducted with a brief (around 5 minutes) open-ended telephone interview. A schedule of assessment for all measures included is presented in Table 1 below.

**Table 1 Tab1:** Schedule of data and measurement collection

Measure	Baseline	During week	At 1 week	During month	At 1 month
Background and pain-related questionnaire	X				
Pain self-efficacy item	X				X
Pain and physical function item	X				X
Mood questionnaire (HADS)	X				
Mindfulness questionnaire (CAMS-R)	X		X		X
Pain-specific questionnaire (BPI)	X				
Pain catastrophizing questionnaire (PCS)	X				X
Health-related quality of life questionnaire (EQ-5D-5L)	X				X
Brief psychological measures (two times, before and after intervention)	X	X			
Experience of audio items			X		
Previous experience			X		
Self-monitoring table		X		X	

HADS, Hospital Anxiety and Depression Scale; CAMS-R, Cognitive and Affective Mindfulness Scale Revised; BPI, Brief Pain Inventory; PCS, Pain Catastrophizing Scale; EQ-5D-5 L, EuroQuol – 5 Dimensions – 5 Levels

### Intervention behaviour change techniques at one week

At one week, the researcher follows up by telephone and encourages continued use of the intervention, identifies perceived barriers and benefits of use and sets goals with the patient by recommending continued use of the intervention at least three times a week. Self-monitoring by diary is also encouraged. These behaviour change techniques come under the labels “Goal setting” or “Action planning”, “Self-monitoring of behaviour” and “Problem solving” as per the Behavior Change Techniques Taxonomy (v1) [37], which is the established standardized taxonomy for behaviour change techniques.

### Debrief at one month

Patients are followed up after one month by telephone for a study debrief. Patients are debriefed regarding the full nature of the study and, if they are part of the control group, they are offered to have the intervention audios sent to them in case they wish to try them. Resources that are readily available to the public are recommended at this time if patients wish to further explore mindfulness. Patients are reminded to complete and post back the questionnaires.

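### The one-month call combines the debrief and the offer of mindfulness audios with the questionnaire reminder, so outstanding one-month forms may be completed after the debrief

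*Protocol article*

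**What the plan says.** The protocol's Debrief at one month section sets out the call: "Patients are followed up after one month by telephone for a study debrief". Four elements belong to it:

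- an explanation of the whole study: "Patients are debriefed regarding the full nature of the study and, if they are part of the control group",
- an offer to those controls: "they are offered to have the intervention audios sent to them in case they wish to try them",
- pointers to further material: "Resources that are readily available to the public are recommended at this time if patients wish to further explore mindfulness",
- a prompt about data: "Patients are reminded to complete and post back the questionnaires".

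The questionnaires go home with the patient on day one. Procedure in clinic describes "The contents of the study packet containing follow-up questionnaires (i.e. Study Diaries 1–3), self-addressed prepaid return envelopes and brief instructions". Study Diary 3 carries the final assessment: "At 1 month, items regarding pain self-efficacy and physical function are repeated in addition to the measures of mood, pain catastrophizing, mindfulness, and HRQoL".

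The Statistical analysis section compares the arms on change from baseline to one month for HADS, EQ-5D-5L, PCS and CAMS-R. It includes everyone with data at both times and says the results are to inform parameters for a definitive trial.

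**The concern.** A reminder to complete a form, and not only to post it, makes sense only if some forms may still be blank. For those patients the plan allows the outcome to be recorded after the researcher has explained the study in full, offered controls the other arm's audios and recommended mindfulness resources.

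Every one-month outcome is a self-report, so it is open to this. Controls told that they had the comparator might rate themselves worse, which would inflate the contrast. Controls who took up mindfulness before answering might rate themselves better, which would dilute it. Treatment patients might answer in line with the hypothesis. The net direction cannot be predicted.

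The stake is the value of the pilot for planning. The Abstract says that feasibility is judged partly by estimating effect sizes. The protocol also prefers one month to one week for functional outcomes because "assessment after the completion of the intervention (one month) will better allow for the detection of changes in function where they have occurred".

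**Working it through.** The protocol states no figure on this point, so there is none to reproduce. The check is mainly a reading of the sections against each other, followed by an illustration of size.

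**1. Can a form be completed after the debrief?** Debrief at one month puts the reminder in the same call as the debrief. If Diary 3 is blank at the call, it will be completed after the whole call, whatever the order of topics within it. Nothing shown requires Diary 3 to be completed first or sets a return window. So late completion is possible for patients with an outstanding form, and the text does not say how many there will be.

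**2. Does the analysis separate such forms?** Statistical analysis includes all participants with data at both times, without regard to completion date. The sensitivity analysis described there is for missing data only.

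**3. Can a late form reflect the period after the call?** The HADS section says that items refer to the previous week. A HADS completed some days after the call therefore partly covers days after the debrief.

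**4. Which outcomes are exposed?** Only those collected at one month. The before-and-after ratings in clinic and in week one, the usefulness and recommendation ratings and the one-week CAMS-R are scheduled before this call.

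**5. Illustrative size.** Let f be the share of one arm completing after the debrief and s the mean shift in those patients in SD units, with no shift in the other arm. The arm mean, and so the contrast, moves by f × s. Both inputs are assumptions.

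| f | s = 0.2 SD | s = 0.5 SD |
|---|---|---|
| 10% | 0.02 | 0.05 |
| 25% | 0.05 | 0.125 |
| 50% | 0.10 | 0.25 |
| 100% | 0.20 | 0.50 |

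For s = 0.3 SD and f from 20% to 50%, the range is 0.2 × 0.3 = 0.06 to 0.5 × 0.3 = 0.15 SD.

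**6. Comparison with sampling error.** Sample size expects around 80 participants with one-month data, or about 40 per arm. The standard error of a standardised difference is about √(2/40) = 0.22 SD, and the 95% half-width is about 1.96 × 0.22 = 0.44 SD (unrounded SE 0.2236). The 0.06–0.15 SD range is below one standard error. In the table, only the 50% and 100% rows at s = 0.5 SD exceed it.

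**7. Effect on planning.** A small bias can still matter, because required sample size varies with 1/d². If an assumed true effect of 0.30 SD were read as 0.20 SD (a shift of 0.10 SD, as at f = 50% and s = 0.2), the calculated size would rise by (0.30/0.20)² = 2.25 times.

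**The case against.** The strongest case against has four parts.

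**The extent of late completion is unknown.** A reader might infer that one-month data in general are collected after the debrief. The documents do not support that. Table 1 schedules the measures at one month, the call comes after one month, and the reminder concerns only forms still outstanding. This stands and limits the point to those patients.

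**Patients are already unblinded.** A reader might infer that the call breaks a blind. It does not: the Randomization section says that participants are not blinded during delivery or outcome assessment, and patients know whether they heard a body scan or a book reading. This weakens the disclosure argument without removing it. A debrief on the full nature of the study suggests that something was held back until then, and the offer made only to controls tells them that the other audio was the one under test. The documents do not say what was held back, so whether controls first learn their role at this call remains conjecture.

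**Contamination needs several steps.** A reader might infer that controls start mindfulness before answering as a matter of course. The audios are sent after the call, so the patient must accept, receive and use them, and only then complete the form. The protocol itself regards one week as probably too short for meaningful change in physical or psychological function. Contamination is therefore the weaker route and depends on a long delay. A reporting shift can act at once.

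**The illustrated bias is mostly smaller than the noise, and the one-month comparison is acknowledged as unlikely to have enough power.** This is correct and lowers the severity. But sampling error is at least expressed in the confidence interval, whereas this bias is not, and the estimates are intended for planning.

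**Conclusion.** The point holds as a procedural weakness of moderate importance. As written, the plan lets patients with an outstanding Study Diary 3 complete the self-reported one-month outcomes after the debrief, the audio offer and the mindfulness recommendations. The result can be a reporting shift in either direction and, with enough delay, some contamination of controls.

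Its size cannot be estimated from the documents. The 0.06–0.15 SD illustration rests wholly on the assumed late share (20–50%) and the assumed shift (0.3 SD in one arm only). The immediate effects, which are a primary objective, and the one-week outcomes are unaffected. The documents do not support a claim that the one-month results are biased by a known amount or that the trial's main conclusions are at risk. The change should be made because it is cheap and because a measurement free of the debrief cannot be recovered once a patient has been debriefed.

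**What to change.** Keep the interview on use, barriers and facilitators and the questionnaire reminder in the one-month call. Give the debrief, the audio offer to controls and the mindfulness resources only after Diary 3 has been received, or after a fixed cut-off for non-returners, by letter or short call. Record the date on which Diary 3 was completed.

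The protocol gives recruitment as ending in June 2016 (Abstract) or July 2016 (Current study status), so some patients may already have been debriefed. For them, report by arm the number of forms completed after the debrief, where dates can be established. An analysis excluding those forms may be shown as exploratory only: late completers are self-selected after randomisation, so the exclusion can introduce bias of its own.

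The cost is one letter or short call per patient, a slightly later offer to controls, and a change to the procedure wording. Sample size and the main analysis stay as they are.

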### Measures

#### Hospital Anxiety and Depression Scale

The HADS is an easily-administered screening questionnaire designed by Zigmond and Snaith [32], which has been widely used as a tool to assess the severity of depression and anxiety. Patients are asked to respond to 14 items, seven measuring anxiety and seven measuring depression. The respondent must choose one of four responses for each item according to how they have felt over the previous week. A score of 0–21 is calculated for each disorder with total scores between 11–21 indicating abnormal levels of anxiety/depression [38]. The HADS has also been routinely used for research within chronic pain populations [39–42].

#### Cognitive and Affective Mindfulness Scale–Revised

The CAMS-R [33] is a revised version of the Cognitive and Affective Mindfulness Scale [43], which is an 18-item measure designed to capture mindfulness as a general daily experience. The CAMS-R is a 10-item scale which uses everyday language appropriate for those with little meditation experience and has been compared with two other existing mindfulness measures, the Mindfulness Attention Awareness Scale [44] and The Freiburg Mindfulness Inventory [45], where it was found to be positively correlated (r = 0.51, *P* < 0.001 and r = 0.66, *P* < 0.001, respectively) [46, 47], with an acceptable internal consistency (a = 0.76) [33], which was a weakness of the original scale. The CAMS-R is unique in that it is related to psychological distress, which is highly relevant to the current study and chronic pain population.

